### Participants

7 schools will take part in the intervention, with students aged 12-13. Schools will be chosen to represent a cross section of demographics, including different ethnic groups and genders. The average year group within Birmingham secondary schools takes approximately 150 students enabling up to 1050 participants in this feasibility trial.

### Ethical approval

The study was granted ethical approval by The University of Birmingham ethics committee in June 2010 (reference number ERN_10-0397), and the primary author is funded through the NIHR CLAHRC (Collaborations for Leadership in Applied Health Research and Care) Birmingham & Black Country programme.

### Development and piloting of the intervention

Original intervention materials were developed by [name], [name] and [name] in collaboration with teachers and service-users with additional educational resources evolved from the work of [name] O'Reilly [62] and the Staffordshire Changes YP mental health programme [63]. Focus groups were also conducted with young people by [name] to aid the development of the programme. Interventions tend to be more successful if they are delivered over time, rather than in one intensive session [9], however the current intervention is a feasibility trial, and due to the constraints of resources, it was decided that a one-day intervention would be used, with the expectation that the intervention will be developed into a longer term intervention plan for evaluation in the future, should it prove to be successful.

The intervention was piloted in one school to assess the practicality; timings, level of pitch, and suitability of materials for the target age group. Classes were randomised to the Education and Contact condition and Education Only conditions. Procedure of the pilot intervention is identical to the feasibility trial.

### Feasibility trial

The feasibility trial intervention covers three interrelated subjects; 1. Stigma of mental illness, 2. Mental health literacy, and 3. Improving our own mental health. Pupils receive four hours aimed to impact upon the former two of these subjects and two hours aimed to impact upon the latter. In the education and contact condition a young person with experience living with mental illness will work with the students as one of the teaching assistants and will lead a 10-20 minute presentation and interactive discussion about living with a mental illness.

The intervention will be delivered by NHS mental health specialist staff and service-users. Training and workshop notes are provided for all individuals prior to their facilitating the interventions to ensure fidelity of implementation. The intervention will be delivered to students in their normal class size and environment.

### Procedure

#### Stage 1; consent and pre-test

Schools in the Birmingham area will be approached and invited to take part in the research, drawn from the full range of socio-economic and socio-cultural settings. Once a school has agreed to participate, consent letters will be sent out to the parents of all participating students.

Pre-intervention questionnaires will be completed 3-4 weeks prior to the intervention day. A self-generated code will be used to match participant answers over time whilst preserving anonymity. This code has a reported 92% success rate [64]. It must therefore be expected that a minimum of 8% of participants may be lost over time due to mistakes in the generation of this code. Teachers will have over a week to collect questionnaire data in order to minimise loss of data through student absences from school.

Class randomisation to condition will take place after pre-test, at the level of school.

#### Stage 2; the intervention

Participants are taught within their usual classes. Each class is facilitated by 2-4 staff including a lead who will be a NHS mental health specialist, and a teaching assistant. Facilitators in the education and contact condition include at least one facilitator who has lived experience of mental illness. As well as the facilitators a minimum of one teacher from the school will be present in each class. Fidelity of the intervention delivery between conditions will be assessed with a pre-developed checklist on the intervention day. One class per condition, per school will be assessed for fidelity by [name]

#### Stage 3; post-tests

Approximately 2 weeks after the intervention day post-intervention questionnaires will be completed by participants, and then again at 6 month follow up.

### Primary outcome measure

#### Stigma of mental illness

The Reported & Intended Behaviour Scale (RIBS) [65] assesses behaviour related to the stigma of mental illness. The RIBS takes around 1-2 minutes to complete and rates participants' willingness to have contact with individuals who are experiencing mental illness (e.g. 'In the future I would be willing to live with someone with a mental health problem'), as well as their current and past experiences (e.g. 'Are you currently living with, or have you ever lived with, someone with a mental health problem?'), though only the former questions generates the participants final score. The RIBS has a test-retest reliability of 0.75, and Cronbach's alpha for items 5-8 (those which generate the participants final score) is 0.85.

### Secondary outcome measures

#### Knowledge of mental illness

Knowledge of mental illness will be assessed in two ways. The Mental Health Knowledge Scale (MAKS) [66] assesses six areas of stigma-related knowledge: help-seeking, recognition, support, employment, treatment, and recovery, takes 1-2 minutes to complete and has a test-retest reliability of 0.71.

Two vignettes will be employed to assess knowledge of mental illness developed by Jorm et al. [67].

#### Emotional well-being

The Strengths and Difficulties Scale (SDQ) [68] will be used to assess the emotional well-being and consists of 25 items which generate scores along five subscales: conduct problems, hyperactivity-inattention, emotional symptoms, peer problems, and pro-social behaviour, as well as producing a total difficulties score. The SDQ has been validated for use with adolescents age 11-16 with a Cronbach's alpha of 0.82 for the total difficulties scale [68].

#### Resilience

Resilience will be measured using a 15 item [69] version of Wagnild and Young's [70] Resilience Scale (Cronbach's alpha of between 0.72-0.94) [71] and concurrent validity is supported by correlations between the Resilience scale and measures of depression, morale, and life satisfaction. The Resilience scale has been used previously in three studies with adolescents [72-74].

#### Help-seeking

Attitudes to help-seeking will be assessed by responses to the question 'In the next 12 months if you were to experience a mental illness, how likely are you to seek help?'

### Exploratory outcome measure

#### Schizotypal thinking

The Schizotypal Personality-Brief Form (SPQ) [75,76] assesses three subscales relating to schizotypal thinking; cognitive-perceptual deficits, interpersonal deficits, and disorganisation. It takes approximately 2 minutes to complete and has an internal reliability of 0.76, a test-retest reliability of 0.90, and has been validated for use with adolescents [77].

### Power and sample size calculation

Assuming an intra-cluster correlation coefficient (ICC) of 0.037 [78] (Aberdeen University: Health Services Research Unit) and a cluster size of approximately 30 students per class, 738 participants would be needed to detect a 0.3 effect size, or 1658 participants to detect a 0.2 effect size. Depending on the size of the included schools, the proposed research will allow for detection of an effect size between 0.3-0.2.

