## Discussion

The strengths of the proposed research are both in its potential for increasing efficacy by the use of contact combined with education to combat primarily stigma, and also in improving mental health literacy and resilience/well-being. Previous research suggests that the intervention may have some effect on stigma even at 6-month follow up, due to this influence of contact combined with education. Pinfold et al. [79] for example, employed contact with an individual with personal experience of living with mental illness in their intervention with 14-15 year old students. Although their intervention was brief, lasting for just two one-hour workshops, a significant positive change in stigmatising attitudes was found both immediately following the intervention and also at 6-month follow up.

Previous interventions have tended to focus on one or at most two of the concepts of stigma, mental health literacy, and resilience/well-being, rather than all three [35-40,42]. This is despite evidence inferring that the three concepts are to some extent interlinked [20,21]. For example, Naylor et al.'s [41] intervention significantly reduced conduct problems and improved prosocial behaviour, despite the fact that the intervention did not contain any features designed to reduce mental illness or promote mental health. Though the research is not directly designed to look at this, if stigma, mental health literacy, and resilience/well-being are interlinked, it may be that by addressing all three simultaneously, a greater impact can be achieved.

The current intervention also addresses many of the methodological issues which have been highlighted by previous systematic research reviews as problematic [9,48]. The study has a high level of power; utilises an active control group; measures and evaluates demographic differences including ethnicity, religion, and gender for response to the intervention; attempts to improve consent rate by utilising an opt-out consent method; is delivered by the research team rather than by teachers from the individual schools and assessed for fidelity of implementation. The research measures mediator variables such as resilience as well as baseline characteristics of the individual such as whether they know someone with a mental illness, and the exact nature and content of the intervention will be explicitly described and freely available.

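### The 0.2 end of the stated detectable range is not supported: on the protocol's own figures the expected sample reaches about 0.25 to 0.26

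*Protocol article*

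**What the plan says.** The section Power and sample size calculation starts from "Assuming an intra-cluster correlation coefficient (ICC) of 0.037" and "a cluster size of approximately 30 students per class". It gives two benchmarks, "738 participants would be needed to detect a 0.3 effect size" and "1658 participants to detect a 0.2 effect size", and then concludes: "Depending on the size of the included schools, the proposed research will allow for detection of an effect size between 0.3-0.2".

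The Participants section gives the only expected sample: "The average year group within Birmingham secondary schools takes approximately 150 students enabling up to 1050 participants in this feasibility trial". This is for seven schools. Stage 1 of the Procedure warns that "a minimum of 8% of participants may be lost over time due to mistakes in the generation of this code". The Discussion adds, without naming an effect size: "The study has a high level of power".

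**The concern.** The two ends of the stated range are the two effects that have just been costed at 738 and 1,658, and school size is named as what moves the trial between them. A reader will take this to mean that, with larger schools, the trial could detect 0.2. The sample expected elsewhere in the article is well short of 1,658, and the article does not say so.

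The closing paragraph presents this feasibility trial as support for larger work. If 0.2 is taken as detectable, a result that is not significant could be read as evidence against an effect of that size, when on the stated calculation a true effect of 0.2 would be missed about 40% of the time.

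**Working it through.** **Inputs from the protocol article.** ICC 0.037, class size about 30, 738 for an effect of 0.3 and 1,658 for 0.2 (Power and sample size calculation); seven schools of about 150, up to 1,050 (Participants); at least 8% lost to code errors (Stage 1). Significance level, sidedness, power and allocation ratio are not stated. I assume two-sided 5%, 80% power and 1:1, and test this against the stated figures.

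**1. Reproducing the stated sample sizes.** Per arm, n = 2(1.960 + 0.842)²/d².
- d = 0.3: 175 per arm, 350 in total.
- d = 0.2: 393 per arm, 786 in total.

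With a design effect of 1 + 30 × 0.037 = 2.11: 350 × 2.11 = 738.5 and 786 × 2.11 = 1,658.5. Both stated figures are matched. The usual form, 1 + (30 − 1) × 0.037 = 2.073, gives 726 and 1,629, within 1.8%, so the choice is immaterial here. One-sided 5% with 80% power (572 and 1,285) and two-sided 5% with 90% power (970 and 2,181) do not reproduce them.

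**2. Required against expected.**
- 1,658 / 1,050 = 1.58.
- 1,658 / 7 = 237 pupils per school, against about 150 stated.
- 1,658 / 150 = 11.05 average-sized schools, against seven.
- Allowing for 8% loss: 1,658 / 0.92 = 1,803 recruited, or about 258 per school.

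**3. Smallest effect detectable with 80% power,** scaled from the protocol's own benchmark, 0.3 × √(738/N). After 8% loss, N = 1,050 × 0.92 = 966.
- N = 1,050: 0.3 × √(738/1,050) = 0.25.
- N = 966: 0.3 × √(738/966) = 0.26.
- N = 738: 0.30. This corresponds to a total loss of 1 − 738/1,050 = 30%.

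**4. Power,** Φ(d / √(4 × DEFF/N) − 1.96), for DEFF from 2.11 to 2.073.

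| Analysed | Power for 0.2 | Power for 0.3 |
|---|---|---|
| 1,050 | about 61% | about 92% |
| 966 | 57–58% | 89–90% |

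**5. What the pre-test covariate could add.** The Analysis section enters the pre-test score as a covariate, but the sample size calculation takes no account of it. Suppose the residual variance scales by 1 − r² and the ICC is unchanged (an assumption). Then 0.2 needs 1,658 × (1 − r²) participants.
- At N = 1,050: r = √(1 − 1,050/1,658) = 0.61, or about 0.60 with the smaller design effect.
- At N = 966: r = √(1 − 966/1,658) = 0.65.
- At r = 0.5 and N = 1,050, power for 0.2 is about 73–74%.

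**The case against.** **The sentence can be read as true.** It may mean only that the sample falls between the two benchmarks, so the detectable effect falls somewhere between 0.3 and 0.2. The values 0.25 and 0.26 do lie inside that interval, and neither benchmark is an arithmetic error. This stands, and it makes the fault one of loose wording. But the lower half of the interval is still not available at the expected sample, and readers are not told.

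**1,050 is not a hard cap.** It is an approximate average multiplied by seven, and the sentence itself makes the result depend on actual school size. A sample somewhat above 1,050 is possible. Reaching 1,658 would need year groups averaging about 237, and nothing in the plan selects schools for size.

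**The planned covariate may bring 0.2 within reach.** It could, at a pre-post correlation of about 0.60. The article quotes a test-retest reliability of 0.75 for the primary scale, which is probably an upper bound for the correlation over the trial interval. So one cannot conclude that 0.2 is unattainable in the planned analysis, or that 61% is the most it can offer. The article does not make this argument, however: its calculation is unadjusted, and its Analysis section introduces the covariate to deal with clustering.

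**A reader might go on to infer that the Discussion's power claim is false.** The documents do not support that. The claim names no effect size, and for 0.3 the power is about 89–92%.

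**Conclusion.** The 0.2 end of the stated range is not supported by the protocol's own calculation. With the expected sample and no covariate adjustment, the detectable effect is about 0.25 at 1,050 and 0.26 after the minimum 8% loss. Power for 0.2 is about 61% and 57–58%. These figures rest on two-sided 5%, 80% power and equal allocation, inferred because they reproduce both stated sample sizes. They also take the stated ICC and class size as given, and allow nothing for opt-outs or absence at follow-up.

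Severity is minor to moderate. The interval contains the true detectable effect, the trial is well powered for 0.3, and no feature of the design or analysis has to change. What needs correcting is a figure the trial states about its own sensitivity.

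**What to change.** Replace the concluding sentence of Power and sample size calculation with: *With 738 to about 1,050 analysed pupils, and without credit for the pre-test covariate, the trial has 80% power (two-sided 5%) to detect an effect of about 0.30 to 0.25; unadjusted power for 0.2 is about 61% at 1,050 and about 57% after 8% loss.* The sponsor should confirm the significance level and power, since both are inferred here.

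If 0.2 is to be kept, state the assumed pre-post correlation and its source, and recompute both benchmarks on that basis.

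The statement in the Discussion need not be withdrawn. At most, tie it to an effect of 0.3.

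The cost is one reworded sentence, an optional qualifier in the Discussion, and a slightly less favourable stated figure.

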### Analysis

Data will be analysed applying appropriate general linear models. In order that the clustering of the sample does not bias the analysis pre-test outcome measures will be entered as a covariate. Subgroup analyses will look at gender, ethnicity, religion, and mental health status of self, family, and friends in relation to the hypotheses and data analysed using appropriate general linear models. Intention to treat analyses will be used.

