**Methods/Design:**

A cluster randomised controlled trial design has been employed to enable a feasibility study of 'SchoolSpace', an intervention in 7 UK secondary schools addressing stigma of mental illness, mental health literacy, and promotion of mental health. A central aspect of the intervention involves students in the experimental condition interacting with a young person with lived experience of mental illness, a stigma reducing technique designed to facilitate students' engagement in the project. The primary outcome is the level of stigma related to mental illness. Secondary outcomes include mental health literacy, resilience to mental illness, and emotional well-being. Outcomes will be measured pre and post intervention, as well as at 6 month follow-up.

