## Method/Design

SchoolSpace is a randomised controlled trial with two conditions: an experimental condition which includes contact with a young person with lived experience of mental illness as well as education, and an active control condition, which includes education but no contact. Measures will be taken 3 weeks prior to the intervention, and at both 2 weeks and 6 months post intervention. Random allocation will take place at the level of school and blocking will be used to randomly stratify classes to different conditions. Random allocation will be independent and concealed. Randomisation will be undertaken by an individual independent of the research team, and will take place after pre-test. The intervention has been designed in accordance with CONSORT guidelines [60,61].

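### The pre-test covariate is named as the safeguard against clustering, but it does not model within-class correlation, so an analysis that follows the sentence understates its standard errors

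*Protocol article*

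**What the plan says.** The abstract describes the design plainly: "A cluster randomised controlled trial design has been employed". Under Method/Design, "blocking will be used to randomly stratify classes to different conditions", and the procedure adds: "Class randomisation to condition will take place after pre-test, at the level of school". Read together, these make the class the unit allocated and the school the block. Delivery follows the same units: "Participants are taught within their usual classes", each class having its own team of two to four facilitators.

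The sample size section takes clustering into account. It uses "Assuming an intra-cluster correlation coefficient (ICC) of 0.037" and "a cluster size of approximately 30 students per class", and arrives at 738 pupils for an effect size of 0.3 and 1658 for 0.2.

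The Analysis section plans general linear models for the outcomes and says of clustering: "In order that the clustering of the sample does not bias the analysis pre-test outcome measures will be entered as a covariate". It names general linear models again for the subgroup analyses. Nowhere does the article mention a random class effect, a cluster-robust variance, generalised estimating equations or a class-level analysis.

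**The concern.** The sentence gives a device and a purpose, and the device does not serve the purpose. Adjusting for a pupil's pre-test score removes only the part of the between-class variation that pre-test scores predict. Pupils in one class still share whatever that class experienced after pre-test: its facilitators, its lived-experience presenter and the discussion on the day. The residuals of pupils in the same class therefore remain correlated, while an ordinary linear model treats them as independent.

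The covariate can even worsen the problem in relative terms. It shrinks the pupil-level residual variance, so the class share of what is left may rise.

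At stake is the RIBS comparison on which the primary hypothesis rests, along with any other outcome analysed in the same way. Confidence intervals would be too narrow, and class-to-class variation could be reported as an effect of contact.

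**Working it through.** **Inputs from the protocol article.** ICC 0.037 and about 30 per class (Power and sample size calculation); 7 schools of about 150, up to 1050 pupils (Participants), hence about 1050/30 = 35 classes, or 5 per school; RIBS test-retest reliability 0.75 (Primary outcome measure). Alpha and power are not stated; two-sided 5%, 80% power and equal arms are assumed.

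**1. Reproduce the plan's own sample size.**

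- Design effect: 1 + (30 − 1) × 0.037 = 2.073.
- Effect size 0.3: 175 per arm before inflation; 2 × 175 × 2.073 = 726, against 738 stated.
- Effect size 0.2: 393 per arm; 2 × 393 × 2.073 = 1629, against 1658 stated.

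Both are about 1.7% below the stated figure. Without the design effect the totals would be 350 and 786. The plan itself therefore treats clustering as roughly doubling the variance.

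**2. Error if the plan's ICC stays in the residual.** The standard error is too small by a factor of √2.073 = 1.44. The true two-sided error of a nominal 5% test is 2 × (1 − Φ(1.96/1.44)) = 17.3%. By residual ICC, at 30 per class:

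| Residual ICC | Design effect | True error |
|---|---|---|
| 0.005 | 1.145 | 6.7% |
| 0.01 | 1.290 | 8.4% |
| 0.02 | 1.580 | 11.9% |
| 0.03 | 1.870 | 15.2% |
| 0.037 | 2.073 | 17.3% |

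**3. Simulate the stated model under no effect.** 7 schools × 5 classes × 30 pupils, with 2 or 3 classes per school in one arm; ordinary linear model with arm and pupil pre-test score; total ICC 0.037 at both times; 4000 runs per scenario. Assumed: pupil-level pre-post correlation 0.5 or 0.75 (the latter borrowed from the RIBS reliability), the correlation of cluster effects between pre-test and post-test, and the share of clustering at school level. Rejection rates at nominal 5%:

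| Cluster-effect correlation | Pupil 0.5, all class | Pupil 0.5, half school | Pupil 0.75, all class | Pupil 0.75, half school |
|---|---|---|---|---|
| 0 | 23.1% | 16.1% | 34.8% | 26.8% |
| 0.5 | 18.2% | 12.4% | 24.9% | 18.9% |
| 0.75 | 13.1% | 9.6% | 19.1% | 11.4% |
| 0.9 | 10.6% | 8.2% | 11.1% | 8.7% |
| 1.0 | 8.8% | 7.6% | 6.8% | 6.0% |

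A class-mean analysis without a school term gave about 4.6% to 6% when all clustering was at class level, but only about 2.5% to 5% when half was at school level.

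**4. Check the extremes by formula** (all clustering at class level, pupil correlation 0.75). With total variance 1 and class-level correlation c, the pre-test slope is b = 0.75 × 0.963 + c × 0.037. The residual class variance is 0.037 × (1 − 2bc + b²), and the residual pupil variance is 0.963 × (1 − 1.5b + b²).

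- c = 0: b = 0.722; class 0.0563, pupil 0.4221; residual ICC 0.0563/0.4784 = 0.118; design effect 1 + 29 × 0.1177 = 4.41; error 2 × (1 − Φ(1.96/2.10)) = 35%.
- c = 1: b = 0.759; class 0.0021, pupil 0.4214; residual ICC 0.0051; design effect 1.147; error 2 × (1 − Φ(1.96/1.071)) = 6.7%.
- c = 0.75: b = 0.75; both variances shrink by the same factor, 1 − 0.75² = 0.4375; the residual ICC stays at 0.037 and the error at 17.3%.

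These agree with the simulation to within about two percentage points. They also show what the 17% means: it applies when class effects are exactly as stable over time as pupils' own scores.

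**The case against.** Much can fairly be said on the other side, though none of it defends the sentence itself.

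- **The article is condensed.** It speaks of appropriate general linear models, and a fuller plan could add a class term. A reader might infer that the covariate is definitely the sole provision and that pupils will certainly be analysed as independent. The article does not establish that; it shows that the one device it names is the wrong one. This remains an error in the text rather than an omission, because a fuller plan would have to contradict the stated rationale to be right.
- **The 17% is not a property of the stated model in general.** It assumes a residual ICC of 0.037, whereas conditioning on pre-test may lower or raise it. This stands.
- **Allocation within schools helps.** It largely balances school-level clustering between the arms. With half of the clustering at school level the simulated range falls to about 6% to 27%. This stands.
- **The ICC is borrowed.** It comes from a cited outside source, and the article does not tie it to RIBS, to this age group or to class rather than school. No ICC is given for the secondary outcomes, so the inflation cannot be sized for them.
- **1050 is a ceiling, and at least 8% loss is expected.** With 30 × 0.92 = 27.6 per class the design effect is 1 + 26.6 × 0.037 = 1.98 and the error 16.4%, which changes little.
- **This is a feasibility trial.** That softens the consequence of a false positive but does not remove it, since the article states a hypothesis of significantly reduced stigma and would build larger work on positive trends.

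**Conclusion.** The concern holds. The Analysis section gives a baseline covariate as the protection against clustering, and that covariate does not provide it. An analysis that follows the sentence yields standard errors that are too small in a trial that allocates whole classes and whose sample size assumes a design effect of 2.073.

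The size is less certain than the direction. It is about 17% in place of 5% if the residual ICC equals the plan's 0.037 with 30 per class, and about 6% to 35% across the simulated scenarios at that total ICC. A reader might infer that the false-positive rate must be far above 5% in every case, and equally so for every secondary outcome. The article does not support that. The inflation would be mild if class effects were almost perfectly stable between pre-test and post-test, or if the residual ICC were very small (6.7% at 0.005). Nothing in the article shows that either condition holds, and class-specific delivery after pre-test gives reason to doubt the first.

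**What to change.** Replace the sentence with wording to this effect: *Outcomes will be analysed with a linear mixed model with a random intercept for class, the unit allocated; school as a fixed stratum term; and the pre-test score as a covariate to gain precision. A small-sample degrees-of-freedom correction (such as Kenward-Roger or Satterthwaite) will be used, as there are about 35 classes.* A class-level analysis with school as stratum would be an acceptable equivalent.

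- Keep the school term. It reflects the blocking, and without it the class-level analysis became conservative (as low as 2.5%) when part of the clustering lay at school level.
- Fit the 2-week and 6-month outcomes separately, or add a pupil random effect if they are modelled jointly.
- For categorical outcomes, name a cluster-appropriate equivalent, since these corrections belong to linear mixed models.
- Apply the same approach to the subgroup analyses.

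The change needs no new data and, for the linear models, only standard software. It brings the analysis into line with the sample size calculation. The price is wider confidence intervals, which are the correct ones.
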